### Statistical methods

Data will be summarized using mean ± standard deviation (SD) or, for non-normally skewed distributions, as median and interquartile range (IQR). Incidence (mild cognitive impairment and cognitive frailty; dementia; recognised pre-frailty conditions; malnutrition; polypharmacy; multimorbidity), prevalence (mild cognitive impairment and cognitive frailty; recognised pre-frailty conditions; malnutrition; polypharmacy; multimorbidity) and mortality among healthy active and physically frail sarcopenic elderly individuals with and without sleep disorders will be compared using chi-square test, adjusted for age and sex.

According to the sample size estimation, 95% CIs will be calculated with Clopper-Pearson method and tested with a test for two proportions. For interpretative purposes multivariable logistic regression will be implemented. Moreover, to evaluate the outcome in terms of continue variable, multivariable ordinal logistic regression model will be used to estimate the association between the sleep disorders and the single unit of decrease in physical and functional score (SPPB score).

Since there will be multiple measures (baseline, + 12 months, + 24 months), the Mixed Model for Repeated Measure (MMRM) will be adopted for the longitudinal analyses.

The analyses will be centralized and performed by the Clinical and Epidemiological Research Unit at University Hospital of Parma using R-Cran and STATA statistical softwares.

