## Methods

### Objectives

Detect, in a comprehensive and translational way, changes in brain, muscle, hormonal milieu, cardiovascular system, skeletal and body composition to gain a deeper understanding of the impact of sleep disorders on mild cognitive impairment and cognitive frailty, sarcopenia and physical frailty, dementia and mobility disability.

The primary objective is to evaluate the effect of sleep disorders on the incidence of physical and functional worsening from the baseline to 12 months [51–53].

The secondary and exploratory objectives are listed in Table 1.

**Table 1 Tab1:** List of secondary and exploratory objectives/outcomes

**Secondary objectives/outcomes** *To be evaluated in healthy active and/or physically frail sarcopenic older individuals with and without SD*
Prevalence and incidence of sarcopenia *according to sex specific cut-points recommended by EWGSOP2* [54]
Prevalence of MCI and cognitive frailty
Effect of sleep disorders on the incidence of MCI and cognitive frailty
Effect of sleep disorders on the incidence of dementia in cognitively frail participants
Prevalence and incidence of recognised pre-frailty conditions (I.e., MCR)
Prevalence and incidence of malnutrition, polypharmacy and multimorbidity
**Exploratory objectives/outcomes** *To be evaluated in healthy active and physically frail sarcopenic older individuals with and without SD*
Radiological, ultrasonographic, and bioimpedance changes in bone, muscle, and body composition
Magnetic resonance and nuclear medicine brain changes
Ultrasonographic and functional cardiovascular system changes
Anthropometric parameters and nutritional measures changes
Quality of life, social well-being, and reward level changes
Use of healthcare services changes
Differences in mortality
Criterion validity between MMSE score and brain MRI/Amyloid PET
Criterion validity between neuropsychological assessment and brain MRI/Amyloid PET
Role of recognised pre-frailty conditions (I.e., MCR) in affecting the adherence to a multi-component treatment

*Abbreviations*: *SD* Sleep disorders, *MCI* Mild cognitive impairment, *MCR* Motoric cognitive risk syndrome, *MMSE* Mini mental state examination, *MRI* Magnetic resonance imaging, *PET* Positron emission tomography

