Our methodological choices, incorporating both subjective and objective measures, as recently recommended by the American Heart Association [128], could comprehensively assess sleep health dimensions and minimize measurement bias. Furthermore, age-adapted analytic procedures we are planning to adopt, could account for interindividual differences and age-related changes in sleep physiology, as highlighted by recent methodological reviews [126].

Anticipated challenges include participant attrition, adherence to sleep monitoring protocols, and potential confounding from comorbidities, psychosocial factors, and medication use. On the other hand, regular follow-up, use of user-friendly wearable devices, robust statistical adjustment for covariates, and optimized sampling frequency represent countermeasures we are planning to involve and which allow to capture sleep variability, and not to miss key biological relationships as well [129, 130].

The project will allow to analyse sleep disorders, a public health problem, in the older population, where it is extremely relevant condition not fully addressed. In particular, reliance on subjective sleep assessment through questionnaires in cognitively frail individuals is known to introduce reporting bias, which can lead to under- or overestimation of sleep disturbances. On the other hand, objective sleep assessment through devices like actigraphs, sleep profilers, and cardio-respiratory monitors can mitigate this bias by providing quantifiable sleep parameters. Therefore, the inclusion of both types of measures, in research and clinical protocols, is known to represent the best opportunity to ensure robust and clinically meaningful assessment of sleep in vulnerable populations, as each provides distinct information: subjective measures reflect perceived sleep quality, while objective measures correlate more closely with sleep architecture. This approach will allow us to assess the sleep misperception, a relevant aspect of sleep health in this population [131–133].

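### The chi-square test named for the secondary incidence and prevalence outcomes and exploratory mortality cannot be adjusted for age and sex as written, and gives no estimate of the sleep-disorder effect

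*Protocol article*

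**What the plan says.** In Statistical methods, the protocol article lists incidence outcomes (MCI and cognitive frailty, dementia, pre-frailty conditions, malnutrition, polypharmacy, multimorbidity), prevalence of the same conditions except dementia, and mortality. It says that these, "among healthy active and physically frail sarcopenic elderly individuals with and without sleep disorders", "will be compared using chi-square test, adjusted for age and sex". It names no stratified test, age bands, regression model or effect measure for them.

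Table 1, under Objectives, sets the targets. Two secondary objectives are causal in wording: "Effect of sleep disorders on the incidence of MCI and cognitive frailty" and "Effect of sleep disorders on the incidence of dementia in cognitively frail participants". Others are descriptive prevalences. Mortality stands among the exploratory outcomes as "Differences in mortality".

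Two other statements touch on adjustment. The next paragraph of Statistical methods, which opens with the test tied to the sample size, adds: "For interpretative purposes multivariable logistic regression will be implemented". It names neither outcomes nor covariates. The Discussion promises "robust statistical adjustment for covariates" without a method. The mixed model for repeated measures is named for the longitudinal analyses.

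**The concern.** There are two faults on the face of the text, and a third that depends on how it is read.

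1. **The adjustment is not executable.** A Pearson chi-square test on a contingency table has no place for age and sex. The analyst must either drop the adjustment or devise one after the data are in. This is a non-randomised cohort aged 65 and over, so age can easily confound incident MCI, dementia and death.
2. **The test does not match the objective.** An objective about the effect of sleep disorders calls for an estimate with a confidence interval. The named test supplies only a p value.
3. **The contrast is open.** The sentence crosses two frailty groups with two sleep groups and does not say which comparison is meant. If it is one test over four cells, a difference between frail and healthy participants alone can make it significant, and that could be reported as a sleep-disorder finding.

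**Working it through.** **Faults 1 and 2** need no arithmetic. The named test has no covariate term and no effect parameter, and nothing else in Statistical methods is tied to these outcomes. The logistic model sits in the primary-endpoint paragraph with its outcomes unstated. The repeated-measures model is not assigned to binary incidence or death.

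**Fault 3**, under the four-cell reading, can be sized only by illustration. The plan states no rate, power or sample size for these outcomes, so there is no figure of its own to reproduce for them.

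Inputs from the Sample size section, all set for the primary outcome:
- N = 300
- frail to healthy 1:1, so 150/150
- with to without sleep disorders 2:1, so 200/100
- rates without sleep disorders of 9% (healthy) and 27% (frail); their mean, (9 + 27)/2 = 18%, matches the stated pooled rate
- risk ratio 1.55
- alpha 5%

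Assumption: the 2:1 split is the same in both strata, giving 100 with and 50 without sleep disorders in each.

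Noncentrality of the 2×4 chi-square (3 df): λ = Σ n_g (p_g − p̄)² / [p̄(1 − p̄)].

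*No sleep effect (9% in both healthy cells, 27% in both frail cells).* p̄ = 0.18 and p̄(1 − p̄) = 0.1476. λ = [150 × 0.09² + 150 × 0.09²] / 0.1476 = 2.43 / 0.1476 = 16.46. Rejection probability is 94% by this formula and 95% in 40,000 simulated trials. All of it comes from frailty.

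*Risk ratio 1.55 in both strata (9%, 13.95%, 27%, 41.85%).* p̄ = 73.8/300 = 0.246 and p̄(1 − p̄) = 0.1855.
- Total: λ = 28.87.
- Frailty (12.3% vs 36.9%): 300 × 0.123² / 0.1855 = 24.47, or 85% of the total.
- Sleep (18% vs 27.9%): (100 × 0.066² + 200 × 0.033²) / 0.1855 = 3.52, or 12%.
- Interaction: 0.88, or 3%.

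Power of the four-cell test is 99.8%, but little of that concerns sleep. In the same simulations a Cochran-Mantel-Haenszel (CMH) test of sleep disorder stratified by frailty rejected in 5.0% of trials with no sleep effect, and in about 50% at a risk ratio of 1.55.

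*Other baseline rates (assumed, since the plan gives none for these outcomes):*

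| Healthy / frail rate | Four-cell rejection, no sleep effect | Frailty share of λ at RR 1.55 |
|---|---|---|
| 10% / 10% | 5% | 0% |
| 8% / 10% | 7% | 25% |
| 8% / 12% | 14% | 52% |
| 5% / 10% | 25% | 74% |
| 5% / 15% | 67% | 85% |
| 9% / 27% | 94% | 85% |

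The size of the third fault thus runs from nothing to nearly complete, depending on how far risk differs by stratum.

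**The case against.** The strongest reply is that this is a condensed article, and that model form, covariates and sparse-event methods normally sit in an analysis plan that is not shown. That stands for details that are merely absent. It does not excuse a method that is stated and cannot be carried out as stated.

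Second, some chi-square tests do adjust: a CMH test over age bands and sex, or a Wald or likelihood-ratio test from a regression. This stands to the extent that the authors may have meant one of these. It would be wrong to say that no chi-square procedure can allow for age. The fault is a misnamed method, and the text names none of the alternatives for these outcomes.

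Third, a reader might infer that the plan commits to a single four-group test with 3 df that mainly detects frail-versus-healthy differences. The documents do not support that. No such test is stated, and the Table 1 heading for secondary outcomes, which allows evaluation in one frailty group or both, also fits comparisons within each group. There the frailty argument falls away. The 9% and 27% are moreover primary-outcome rates taken from two different endpoints, and the cell layout cannot apply to the dementia objective, which is limited to cognitively frail participants.

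Fourth, a reader might infer that the plan contains no adjusted effect estimate at all. That too goes beyond the text: the logistic model is not ruled out for these outcomes. It is simply not assigned to them.

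Finally, the sentence also covers prevalence, where a plain descriptive comparison can suit the objective.

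**Conclusion.** The point holds in limited form. The age- and sex-adjusted chi-square comparison is not an executable specification, and it yields no estimate of the sleep-disorder effect that Table 1 asks for. Both faults remain whether the comparison is read as four cells, as within stratum, or as with versus without sleep disorders overall. The last reading would in addition be confounded by frailty if the prevalence of sleep disorders differs between strata.

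The risk of mistaking a frailty difference for a sleep effect is conditional. It requires the four-cell reading and unequal risks by stratum. The 94-95% figure rests on both, on borrowed primary-outcome rates and on an equal 2:1 split in each stratum.

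The affected results are secondary (incidence and prevalence) and exploratory (mortality). The primary analysis is untouched. The wording should be corrected before analysis begins.

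**What to change.** Replace the sentence with a regression model for each binary outcome. The logistic model already named in Statistical methods would do, or modified Poisson regression with robust variance if a risk ratio is wanted. Enter sleep disorder as the exposure and SPPB stratum, age and sex as covariates, and report the adjusted odds or risk ratio with its 95% CI.

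In addition:
- restrict each incidence model to participants free of that condition at baseline;
- use a penalised or exact method where events are few, as may happen for dementia and death;
- fit a sleep-by-stratum interaction only where events permit.

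A CMH test stratified by SPPB stratum, sex and age band is an acceptable simpler alternative, provided the bands are fixed in advance and the common odds or risk ratio is reported with its interval.

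The cost is a few lines of protocol or analysis-plan wording and routine code in R or Stata, both of which the plan already uses. No extra data are needed: age, sex, SPPB and sleep status are all collected at baseline.

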### Sample size

An overall sample size of 300 patients was defined according feasibility.

However, according with the primary endpoint and the study design, the statistical power estimation was performed.

More specifically, we simulated the width from the lower limit of 95% confidence intervals for the Ratio Between Two Proportions.

The following parameters and assumptions were included into the equation:overall sample size of 300 patients;assumption of the balanced numbers (1:1) of physically frail sarcopenic [3 ≥ SPPB score ≤ 8] and healthy active elderly [SPPB score > 8] individuals;assumption of the unbalanced numbers (2:1) of individuals with and without sleep disorders at the baseline;expected rate of 9% of SPPB score < 9 at 12 months in healthy active elderly individuals [SPPB score > 8] without sleep disorders [118–123];expected rate of 27% of inability to complete a 400 m walk test in less than 15 min (without sitting, stopping for more than one minute, receiving help, or using a walker) in physically frail sarcopenic elderly individuals [3 ≥ SPPB score ≤ 8] without sleep disorders [18];an overall risk ratio of 1.55 at 12 months for individuals with sleep disorders versus the ones without sleep disorders (pooled expected rate 18%);an alpha error of 5%;

Thus, to reject the null hypothesis the lower limits of the ratio must not be lower than 1.11 (corresponding to a 20% of the lower limit of the differences).

Participants will be enrolled at the Frail elderly lab of the Geriatric Clinic Unit within the Interagency integrated activity department of continuity and multicomplexity of the University Hospital of Parma, by acquisition of informed consent and if, upon the geriatric multidimensional assessment, the eligibility criteria given in this study protocol will be met.

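### The interval named for the primary comparison gives no risk-ratio limit, and the two-proportion test, with no null ratio stated, can contradict the 1.11 rejection rule in the sample size section

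*Protocol article*

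**What the plan says.** Two sections of the protocol article bear on how the 12-month primary comparison is decided.

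- **Sample size.** The planning quantity is a ratio: "we simulated the width from the lower limit of 95% confidence intervals for the Ratio Between Two Proportions". The decision rule is set on that ratio: "to reject the null hypothesis the lower limits of the ratio must not be lower than 1.11". The total of 300 comes from feasibility, with a 2:1 split by sleep disorder and a 1:1 split by frailty group. The expected rates without sleep disorders are 9% and 27% in the two frailty groups, the pooled rate is 18%, the risk ratio is 1.55 and alpha is 5%. Sidedness is not stated.
- **Statistical methods.** The sentence opens by tying itself to the sample size estimation and continues: "95% CIs will be calculated with Clopper-Pearson method and tested with a test for two proportions". It does not say which quantity the intervals are for, gives no null ratio and does not mention 1.11. Logistic regression is added for interpretation only.

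**The concern.** The second section claims to carry out the first, but the method it names does not deliver what the first needs. Clopper-Pearson gives an exact interval for a single binomial proportion, so it yields one interval per exposure group and no limit for their ratio. The rejection rule is a statement about that ratio limit.

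The accompanying test raises a second problem. A two-proportion test with no stated null is normally read as a test of equality, that is, of a risk ratio of 1. The Sample size section asks for more: a lower limit of at least 1.11. A result can then be positive under one section and negative under the other. At stake is the conclusion on the primary outcome, because the choice between the rules would remain open after the data are seen.

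**Working it through.** **Inputs, all from Sample size.** N = 300 ("An overall sample size of 300 patients was defined according feasibility"). Exposure split: "assumption of the unbalanced numbers (2:1) of individuals with and without sleep disorders at the baseline", so 200 versus 100. Frailty split 1:1, so the unexposed rate averages (9% + 27%)/2 = 18%, which matches the stated pooled rate. With a risk ratio of 1.55 the exposed rate is 1.55 × 18% = 27.9%.

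**Assumptions added here.** 18% is the unexposed rate (the alternative is shown below); no dropout; two-sided 5%; log-method interval, unstratified unless stated; pooled-variance z test of equality. The article names neither a ratio interval nor a form of the two-proportion test.

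**Step 1: the plan's own figure.** The log-method lower limit is RR × exp(−1.96 × √(1/x1 − 1/n1 + 1/x0 − 1/n0)). At the planned inputs, x1 = 55.8 of 200 and x0 = 18 of 100:

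1.55 × exp(−1.96 × √(1/55.8 − 1/200 + 1/18 − 1/100)) = 1.55 × exp(−1.96 × 0.2418) = 0.965.

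The 1.11 does not reproduce as a confidence limit. Variants with one- or two-sided limits, 2:1, 1:2 or 1:1 allocation and other readings of 18% range from 0.874 to 1.083; a Mantel-Haenszel ratio over the two frailty groups gives 0.980. However, 1 + 0.20 × (1.55 − 1) = 1.11, so the figure looks like a threshold at 20% of the assumed excess risk. That is an inference. Where 1.11 comes from is a separate sample-size question; here it matters only that it is worded as the condition for rejection.

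**Step 2: what Clopper-Pearson gives.** The limits are the Beta(x, n−x+1) 2.5% quantile and the Beta(x+1, n−x) 97.5% quantile. For 56/200 they are 0.219 and 0.348; for 18/100 they are 0.110 and 0.269. These are two separate intervals. Dividing one limit by another (0.219/0.269 = 0.81) is not a 95% limit for the ratio; the log method gives 0.969 for the same data.

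**Step 3: the two rules on the same data.** The test statistic is z = (p1 − p0)/√(p(1−p)(1/200 + 1/100)), with p the pooled proportion. For 60/200 versus 18/100: p = 78/300 = 0.26 and z = 0.12/√(0.26 × 0.74 × 0.015) = 2.234, so p-value = 0.026. RR = 0.30/0.18 = 1.667 and the lower limit is 1.667 × exp(−1.96 × 0.2392) = 1.043. With 18/100 unexposed events throughout:

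| Exposed events /200 | RR | p, test of equality | Lower limit of RR | Test | 1.11 rule |
|---|---|---|---|---|---|
| 56 | 1.556 | 0.058 | 0.969 | no | no |
| 57 | 1.583 | 0.048 | 0.987 | reject | no |
| 60 | 1.667 | 0.026 | 1.043 | reject | no |
| 63 | 1.750 | 0.013 | 1.099 | reject | no |
| 64 | 1.778 | 0.010 | 1.117 | reject | reject |

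Every count from 57 to 63 gives opposite conclusions. At 57 the log interval even includes 1 while the test is significant, which shows why the test and the interval should be a matched pair.

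**Step 4: how often this happens.** Exact binomial enumeration over all outcomes of 200 and 100, counting rejections in the direction of harm:

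| Scenario | Test of equality | Lower limit ≥ 1.11 | Rules disagree |
|---|---|---|---|
| 18% unexposed, 27.9% exposed | 46.9% | 25.6% | 21.3% |
| 18% overall (unexposed 0.54/4.1 = 13.17%, exposed 20.41%) | 33.3% | 17.5% | 15.8% |
| No effect, 18% in both groups | 2.3% | 0.7% | 1.7% |

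In each scenario every disagreement has the test positive and the 1.11 rule negative. The two rules also run at different error levels.

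**The case against.** The strongest reply is that the Statistical methods sentence never says the Clopper-Pearson interval is for the ratio. The primary outcome is an incidence, for which an exact interval in each group is sound, and a condensed article may leave the ratio method to the full plan. Part of this stands: Clopper-Pearson has a proper descriptive use here. It does not remove the problem, because the sentence ties the interval to a sample size estimation that rests on a ratio, and the 1.11 limit is worded as the condition for rejecting the null. This is a mismatch between named methods, not an omitted detail.

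Four stronger readings go beyond the documents:

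- A reader might infer that the trial cannot compute its own criterion. It can: a risk-ratio limit follows from the same 2×2 table once a method is named.
- A reader might infer that the article fixes the test's null at a ratio of 1. It states no null. A two-proportion test can be run against 1.11, and with its matching interval the rules would then agree. Equality is only the usual default.
- A reader might fear a decision by non-overlap of the two Clopper-Pearson intervals. No section proposes that; a test is named.
- A reader might see the logistic model's odds ratio as a further contradiction. The model is for interpretation only and decides nothing.

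**Conclusion.** The concern holds in this limited form. The interval named for the primary comparison does not produce the ratio limit on which rejection is said to rest, and the accompanying test has no stated null and, read in the usual way, can contradict the 1.11 rule. At the plan's own effect size the two rules part in about 21% of studies if 18% is the unexposed rate, or about 16% if it is the overall rate. Both figures assume 200 versus 100 participants with complete follow-up, a two-sided 95% log-method interval and a test of equality; another ratio interval or a stratified analysis would move them somewhat. The low rejection probabilities are a sample-size matter and are not part of this point.

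**What to change.** In Statistical methods, name a risk-ratio interval for the 12-month primary comparison (for example a Miettinen-Nurminen or Koopman score interval, or a log-based one), and state the null ratio and the sidedness. Use that single rule in both sections, with a test that matches the interval.

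- If the null is a risk ratio of 1, restate 1.11 as a separate relevance threshold read from the same interval, or remove it.
- If 1.11 stays as the rejection limit, test against a ratio of 1.11.

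Which of the two applies is for the sponsor to decide, before outcome data are examined. Keep Clopper-Pearson for incidence within each group. The logistic model can stay as a supporting analysis; no new primary model is needed.

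The cost is a wording change in the protocol and the analysis plan, with no change to data collection or visits.

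### The primary comparison is a two-proportion test with no adjustment named, pooled over two frailty groups with planned risks of 27% and 9%, so its risk ratio is biased if sleep-disorder prevalence differs between the groups

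*Protocol article*

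**What the plan says.** All references are to the protocol article.

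- **Design.** Study design describes a prospective cohort in which sleep disorder is the exposure. Nothing is randomised.
- **Outcome.** The Outcomes section defines 12-month worsening as a different event in each group: an SPPB score below 9 in healthy active participants, and failure of the 400 m walk in physically frail sarcopenic participants.
- **Planned risks.** Sample size gives, for participants without sleep disorders, "expected rate of 9% of SPPB score < 9 at 12 months in healthy active elderly individuals" and "expected rate of 27% of inability to complete a 400 m walk test in less than 15 min". It then works with one overall risk ratio of 1.55 on a pooled rate of 18%.
- **Planned mix.** "overall sample size of 300 patients", with "assumption of the balanced numbers (1:1) of physically frail sarcopenic" and healthy active participants, and "assumption of the unbalanced numbers (2:1) of individuals with and without sleep disorders at the baseline". The 2:1 ratio is not given by SPPB group.
- **Primary test.** Statistical methods follows the sample size set-up: Clopper-Pearson intervals, and the comparison is "tested with a test for two proportions". On regression it says "For interpretative purposes multivariable logistic regression will be implemented".
- **Adjustment elsewhere.** Adjustment for age and sex is attached to a list of other incidences, prevalences and mortality. The primary outcome is not on that list. The Discussion offers "robust statistical adjustment for covariates" among its countermeasures to anticipated problems, which include confounding.

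**The concern.** Baseline SPPB group determines which event is counted and, on the plan's own figures, triples the risk. The Background also says that sleep anomalies are associated with frailty. A variable tied to both exposure and outcome confounds their comparison, and the test named for the primary outcome does not account for it. Recruitment may strengthen the link: Setting and participants draws on geriatric clinics, sleep clinics and earlier studies, and these sources may differ in both exposure and frailty.

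At stake is the study's main estimate. Part of the reported ratio could reflect the mix of frail and healthy participants in the exposed and unexposed groups rather than any effect of sleep disorders. The bias can run either way, so it could also hide a real effect.

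**Working it through.** **1. Reproduce the pooling.** With groups of equal size, (9% + 27%)/2 = 18%, which is the article's pooled rate. The exposed risk is 0.18 × 1.55 = 27.9%. This supports reading the planned comparison as one pooled ratio over both SPPB groups.

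**2. Inputs.** From Sample size: 150 frail and 150 healthy active; 200 exposed and 100 unexposed; risks 0.27 and 0.09. Assumed, because the article does not give it: how the 200 exposed divide between the groups. Let *f* be the number of exposed frail participants. The exposed then comprise *f* frail and 200 − *f* healthy, and the unexposed 150 − *f* frail and *f* − 50 healthy.

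**3. Expected crude ratio with no true effect.**

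- Exposed risk = [0.27*f* + 0.09(200 − *f*)]/200
- Unexposed risk = [0.27(150 − *f*) + 0.09(*f* − 50)]/100

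For *f* = 120: exposed (32.4 + 7.2)/200 = 0.198; unexposed (8.1 + 6.3)/100 = 0.144; ratio 1.375.

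**4. False rejection.** Simulation with 200,000 runs per row and no true effect. The fourth column is the pooled two-proportion z test at two-sided p<0.05. The fifth requires the lower 95% limit of the ratio to be at least 1.11, as Sample size states; the Katz log interval used for it is an assumption. The last column is a Mantel-Haenszel test stratified by SPPB group.

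| Exposed frail / healthy | Prevalence frail / healthy | Crude RR | p<0.05 | Lower limit ≥ 1.11 | Mantel-Haenszel |
|---|---|---|---|---|---|
| 90 / 110 | 60% / 73% | 0.86 | 9% | 0.1% | 5% |
| 100 / 100 | 67% / 67% | 1.00 | 4% | 0.6% | 5% |
| 105 / 95 | 70% / 63% | 1.08 | 5% | 1% | 5% |
| 112 / 88 | 75% / 59% | 1.20 | 9% | 3% | 5% |
| 120 / 80 | 80% / 53% | 1.375 | 19% | 8% | 5% |
| 125 / 75 | 83% / 50% | 1.50 | 29% | 14% | 5% |

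In the first row, nearly all rejections at p<0.05 are in the direction of apparent benefit. From 75%/59% downward, nearly all are in the direction of harm.

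**5. With a true ratio of 1.55 in each group.** The expected crude ratio is 1.55 at equal prevalence, 1.55 × 1.2045 = 1.87 at 75%/59%, and 1.55 × 1.375 = 2.13 at 80%/53%. Power at equal prevalence is about 47% for the crude test and 50% for Mantel-Haenszel. At 80%/53% the crude test rejects in about 90% of runs and Mantel-Haenszel in about 42%.

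**The case against.** - **The size rests on an assumed prevalence gap.** This stands. The article supports a direction (sleep anomalies go with frailty), not a size. Sleep-clinic attenders could supply many exposed healthy active participants and shrink or reverse the gap. A small gap does little: at 70%/63% the ratio is 1.08 and rejection is about 5%.
- **The decision rule is not p<0.05 against a ratio of 1.** This also stands. Under the 1.11 lower-limit rule, false rejection is about 3% at 75%/59% and 8% at 80%/53%, instead of 9% and 19%. The bias in the estimate is the same under either rule.
- **The article never calls the test unadjusted or unstratified.** True; this is inferred from the pooled sample size set-up and from the absence of any adjustment attached to the test. It is nevertheless the analysis that the article states, so the point is not one of detail left to an unseen analysis plan.
- **Adjusted analyses are planned.** Multivariable logistic and ordinal models and a mixed model for repeated measures are all named. A reader might infer that the methods contradict the Discussion. They do not: the Discussion promises adjustment in general terms and adjusted estimates will exist. The mismatch is that adjustment has only a supporting role for the primary outcome.
- **A reader might also infer that sleep disorders will look harmful whenever they are commoner in frail participants.** That is too absolute. It holds for the expected crude ratio when there is no true effect. With a true ratio of 0.8 at 73%/60% the expected crude ratio is 0.8 × 1.167 = 0.93, and chance can reverse the sign in any one study.

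**Conclusion.** The point holds. As stated, the primary comparison gives a risk ratio confounded by baseline SPPB group unless sleep disorders happen to be equally common in the two groups, and nothing in the design makes them so. The article does not allow the size or even the sign of the bias to be fixed. Over the assumed range, the crude ratio with no true effect lies between 0.86 and 1.50, and the top of that range is close to the planned effect of 1.55. The direction suggested by the Background is upward. These figures depend on the planned risks of 9% and 27%, the 150/150 and 200/100 splits, and the assumed prevalences; the rejection rates also depend on which decision rule is applied.

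**What to change.** Make the primary estimate a risk ratio stratified by, or adjusted for, baseline SPPB group. A Mantel-Haenszel risk ratio is enough. Adjust for at least age and sex in a regression, either as the primary model or in support of it. Report the risk ratio within each SPPB group, since the events differ, and present the crude pooled comparison as descriptive. State this before outcome data are analysed. The choice of regression model and any longer covariate list can be left to the analysis plan.

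The cost is a change of wording and little extra analysis: SPPB group, age and sex are already recorded. At equal prevalence no power is lost (about 50% against 47%). Under imbalance the stratified test rejects less often than the crude one (42% against 90% at 80%/53% with a true ratio of 1.55), but the crude test's excess there comes from bias and is not usable power.
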